#### Categorical predictors

Educational interventions after 1 year in two arms, and an arm with standard care (control), age and gender.

#### Test statistics for primary outcome and dependent variable

The effect of the educational interventions will be evaluated using two-level logistic regression models with a dependent binary variable (case-control, cross-sectional analysis), with patients nested within practices.

Data regarding hospitalization will be collected directly from patient electronic health records held by the National Health Fund (NHF—the state health insurance system). Patients registering exacerbation, defined as “hospitalization of patients with the J-44 as a main reason for admission,” will be classed as cases. Control subjects will be collected from electronic health records held by the NHF, defined as COPD (J-44), age over 65, with low treatment cost, and no constantly reimbursed drugs. Data will be collected after the 1-year study period (cross-sectional) within the Lodz voivodeship.

Descriptive statistics and logistic regression will be employed. The level of statistical significance will be *p* < 0.05.

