## Contribution to the literature

This document describes the design and implementation of a pragmatic study to assess the effectiveness and implementation of a strategy based on a structured checklist in primary care.The impact of the checklist on care in COPD will be determined using Big Data methods.The clinical effectiveness of repetition of COPD checklist exposure in primary care will be assessed.

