### Sample size

A minimum number of 84 GP clinics with at least 30 J-44 patients per clinic is required to provide a sufficient sample size for a three-arm cluster randomized controlled trial: 84 clusters and at least 2520 subjects are needed (28 clusters in each study arm) to detect a difference of 0.026 between mean event rates of hospitalization with ICD-10 code J-44 as the main reason for admission. This assumes a 25% reduction in total number of events after the intervention in the first arm (receiving checklist once) and 50% reduction in total number of events after the interventions in the second arm (receiving checklist twice) compared to the control group not receiving any intervention (standard care). It is also assumed the tests will have 80% power, a two-tailed alpha of 0.05, and intra-cluster correlation of 0.01.

Data collected from electronic health records in 2016 indicate that the mean event rate of “hospitalized with ICD-10 code J-44 as the main reason for admission” in the control group is 0.105, and the standard deviation is 0.306. The unadjusted sample size was calculated for differences between three means for one-way ANOVA.

To compare the individuals hospitalized with the J-44 code in the three arms after 1 year, the difference between the mean event rates of the three groups was calculated according to Donner and Klar [16].

A standard sample size formula was used to calculate the initial unadjusted sample size requirements, followed by appropriate adjustment for clustering by general practice according to Campbell et al. [17], with expected small clustering effect (ICC = 0.01) [18, 19].

To prevent loss to follow-up among practices/participants, an enlarged overall sample size will be deemed appropriate to ensure adequate power.

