### Randomization

The clinics will be randomized without repeating by a Data Scientist (not involved in the trial) using a computer system. Each GP clinic will be allocated randomly to one of three equal-sized arms: two intervention arms and a control arm by Data Scientist.

The clinics from the intervention arms will find out that they are enrolled when they receive the letters with interventions. The letters will be sent simultaneously. The control arm will only use usual care and has no intervention.

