### Outcomes

*The primary outcome of the study* will be the effect of the interventions on the proportion of “hospitalization with the J-44 code as a main reason for admission,” and the proportion of deaths of elderly COPD patients, registered within practices after 1 year.

*Primary outcome at the patient level* will be assessed as the proportion of cases between the three arms (intervention 1, intervention 2 and control) at the end of the 1-year study period. Proportion of cases (event rates) of binary variables of exacerbation outcome will be assessed based on “hospitalization with the J-44 code as a main reason for admission,” and the proportion of deaths of elderly COPD patients.

The effect of the educational intervention will be evaluated using logistic 2-level regression analysis, based on odds ratios (OR) and 95% confidence limits.

We will examine the association between intervention and COPD exacerbation, using a case-control approach. Cases will be selected among COPD exacerbation after 1 year. Control subjects will be selected among COPD patients.

*Secondary outcome at the patient level* will be the proportion of the control and intervention arms regarding the specific short- and long-acting drugs prescribed after 1 year.

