## Discussion

Our methods will be used to quantitatively evaluate the impact of the proposed educational program on reducing COPD exacerbations among COPD patients presenting at primary care clinics compared with existing standard care.

Its main limitations relate to the specificity and sensitivity of the COPD coding, gaps in databases, and short period of observation. In addition, some selection bias may exist in the study, since small practices will be excluded. Furthermore, the COVID epidemic could also distort the effects of the intervention and influence the results. Finally, the participation of the National Health Fund and the sending of letters may be disrupted.

Nevertheless, we believe that the results will be directly relevant and applicable to primary care in Poland. If the implementation is effective, then wide-scale application would be warranted. We will consider additional data collection time points to extend further analysis to account for the impact of COVID.

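### Two unranked primary outcomes and two checklist arms share one level of p < 0.05; the 5% used for sizing belongs to a single three-group test on hospitalization

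*Protocol article*

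**What the plan says.** All places are in the Protocol article.

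- **Outcomes.** The primary outcome "will be the effect of the interventions on the proportion of" J-44 admissions, "and the proportion of deaths of elderly COPD patients, registered within practices after 1 year". The two proportions are not ranked and are not called a composite. Effects are to be given as odds ratios with 95% limits from a two-level logistic model.
- **Objectives, Trial design, Categorical predictors.** Two checklist arms (one delivery, two deliveries) are compared with usual care, and arm enters the model as a categorical predictor.
- **Randomization.** "Each GP clinic will be allocated randomly to one of three equal-sized arms".
- **Test statistics for primary outcome and dependent variable.** "The level of statistical significance will be" *p* < 0.05. No main contrast, order, split of alpha or overall test is named.
- **Sample size.** "It is also assumed the tests will have 80% power, a two-tailed alpha of 0.05, and intra-cluster correlation of 0.01". The unadjusted size comes from a one-way ANOVA on three means, for hospitalization only.
- **Contribution to the literature.** "The clinical effectiveness of repetition of COPD checklist exposure in primary care will be assessed". This implies a twice-versus-once question, though no section specifies a test for it.

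**The concern.** The design controls 5% for one overall test of three arms on one outcome. The analysis produces an odds ratio for each checklist arm against the same control, and the Outcomes section makes two outcomes primary. The same threshold of 0.05 applies to each result. The arms are one and two deliveries of the same checklist, so success in either would be read as support for one idea. It is therefore hard to argue that the two contrasts are unrelated questions needing no joint error control.

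The Discussion says: "If the implementation is effective, then wide-scale application would be warranted". It does not say in which arm, or on which outcome, the implementation has to be effective. A reader of the results could not tell whether an isolated significant odds ratio counts as the trial's answer.

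**Working it through.** **1. The plan's own figure.** Inputs from Sample size: control rate 0.105, SD 0.306, reductions of 25% and 50%, ICC 0.01, 30 patients per clinic, 28 clinics per arm.

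- Expected rates: 0.105; 0.105 × 0.75 = 0.07875; 0.105 × 0.50 = 0.0525.
- Effect size: f² = (2 × 0.02625² / 3) / 0.306² = 0.000459 / 0.093636 = 0.0049.
- A three-group F test at 0.05 with 80% power needs 656 per arm.
- Design effect: 1 + 29 × 0.01 = 1.29, so 656 × 1.29 = 846 per arm, 28.2 clinics per arm and 2539 patients in total. The plan states 2520, a 0.7% difference.

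The sample size is therefore reproduced as that of one overall test on hospitalization at 0.05.

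**2. Error rate if contrasts are tested separately.** No effect in any arm, equal arms, shared control, z = difference / √2 in units of one arm's standard error, 2 million simulated draws. The two contrasts with control correlate at 0.5. The correlation between the hospitalization and death results is not given in the document, so it is varied as an assumption.

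Chance of at least one two-sided *p* < 0.05:

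| Tests | Correlation 0 | 0.5 | 1 |
|---|---|---|---|
| 1 outcome, 2 contrasts with control | 9.0–9.1% | same | same |
| 1 outcome, 3 pairwise contrasts | 12.2% | same | same |
| 2 outcomes, 2 contrasts each | 17.3% | 16.1% | 9.1% |
| 2 outcomes, 3 contrasts each | 22.9% | 21.3% | 12.2% |

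Hand check for independent outcomes: 1 − (1 − 0.0903)² = 0.172 and 1 − (1 − 0.122)² = 0.229.

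**3. False benefit only.** Counting only results that favour a checklist over usual care:

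- One outcome: 4.5%.
- Two outcomes: 8.1% (correlation 0.5) to 8.8% (correlation 0).
- One two-sided test at 0.05, for comparison: 2.5%.

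**4. Overall test per outcome.** If each outcome were judged by one three-arm test, the chance of a false positive is 5.0% for one outcome and up to 9.8% for two (independent case: 1 − 0.95² = 9.75%).

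**5. Power of the single contrasts on hospitalization.** Effective size per arm is 840 / 1.29 = 651. With the stated SD, the standard error of a difference is 0.306 × √(2/651) = 0.01696.

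- Twice versus control: 0.0525 / 0.01696 = 3.10; Φ(3.10 − 1.96) = 87%. With binomial variances, 94%.
- Once versus control: 0.02625 / 0.01696 = 1.55; Φ(1.55 − 1.96) = 34%. With binomial variances the standard error is √[(0.105 × 0.895 + 0.07875 × 0.92125) / 651] = 0.0160, giving z = 1.64 and Φ(1.64 − 1.96) of about 37–38%.
- Twice versus once: the same expected difference, 0.07875 − 0.0525 = 0.02625, so again about 34% with the stated SD.

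**The case against.** The strongest reply is that the document never says each contrast is a separate confirmatory test. The sizing points to one overall three-arm test, and with exactly three groups a significant overall test followed by unadjusted pairwise tests does hold 5% for one outcome. Order and adjustment are also commonly left to an analysis plan, which is not shown here. This stands in part: on that reading the rate falls to 5–10%. But no such gate is stated, and with two unranked primary outcomes it would still generally exceed 5%. What the article does fix, namely two primary proportions, two arms against control and one threshold, does not deliver the 5% used for sizing.

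It is also fair to say that death may never be tested as primary. The section on statistical methods lists hospitalization and medication, and the test section defines cases by hospitalization alone, with no model for death. That leaves the status of death unsettled, and the Outcomes section still calls it primary.

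A reader might infer three stronger things that the document does not support:

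- That there is a 9–23% chance of falsely claiming that a checklist works. Those rates count false findings of harm as well as benefit.
- That 23% is the rate against usual care. It needs a twice-versus-once test, which the stated aims imply but no section specifies, and independent outcomes. Against usual care the ceiling is about 17%.
- That any one significant result would trigger roll-out. The sentence in the Discussion is a general remark, not a decision rule.

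**Conclusion.** The point holds in a limited form. As written, the testing scheme does not carry the 5% error rate assumed in the sample size. If each contrast with control is tested separately, the two-sided rate is roughly two to three and a half times nominal, and the rate of false benefit against usual care is about two to three and a half times its 2.5%.

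These figures rest on no true effect in any arm, equal arms with a shared control, normal test statistics and an assumed range for the correlation between the two outcomes. They also rest on reading the contrasts as separate tests, which the text allows but does not state. The sample size arithmetic itself is sound for the overall test.

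**What to change.** Add one paragraph to the analysis section, dated before data extraction (scheduled from March 2021):

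- J-44 hospitalization, the outcome used in the aim and the sample size, is the sole primary outcome. Death is secondary.
- Testing on that outcome follows a fixed order, each step at two-sided 0.05: (1) twice versus control; (2) once versus control, only if step 1 is significant; (3) twice versus once, only if step 2 is significant.
- All other tests are descriptive, with odds ratios and 95% limits.

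The order follows the plan's own assumption of a larger effect in the twice arm, and alpha is not split. By comparison, Bonferroni over two outcomes and two contrasts (0.05 / 4 = 0.0125) would leave hospitalization power at 73% for twice and 17% for once versus control.

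The cost is that once versus control cannot be claimed if step 1 fails. That is fairly unlikely under the plan's assumptions (step 1 power about 87–94%). The larger limitation is step 2, with about 34–38% power even unadjusted. A single-checklist claim will therefore often not be reached, nor will step 3 behind it. The sponsor should accept this openly when adopting the order, since it comes from the sample size and not from the ordering.

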## Discussion

Our methods will be used to quantitatively evaluate the impact of the proposed educational program on reducing COPD exacerbations among COPD patients presenting at primary care clinics compared with existing standard care.

Its main limitations relate to the specificity and sensitivity of the COPD coding, gaps in databases, and short period of observation. In addition, some selection bias may exist in the study, since small practices will be excluded. Furthermore, the COVID epidemic could also distort the effects of the intervention and influence the results. Finally, the participation of the National Health Fund and the sending of letters may be disrupted.

Nevertheless, we believe that the results will be directly relevant and applicable to primary care in Poland. If the implementation is effective, then wide-scale application would be warranted. We will consider additional data collection time points to extend further analysis to account for the impact of COVID.

## Trial status

The trial is currently in the interventions phase.

ClinicalTrial.gov identifier: NCT04301505. Registered on 10 March 2020, https://clinicaltrials.gov/ct2/show/NCT04301505

Protocol Version 9: 16 January 2021.

Date recruitment began: March 2020.

Estimate of the date when recruitment will be completed: March 2021.

## Data Availability

Not applicable.

## Abbreviations

CME: Continuing medical education
COPD: Chronic obstructive pulmonary disease
CRCT: Cluster randomized controlled trial
ICD-10: International Classification of Diseases
NFZ: National Health Fund
GP: General practitioner
PC: Primary care
EHRs: Electronic health records
TICD: Tailored Implementation for Chronic Disease
